Our cohort will consist of at least 60 pediatric primary care practice sites from at least 6, diverse practice groups: Cleveland Clinic Children's, Dartmouth Medical Center, Johns Hopkins Harriet Lane Clinic, Medical University of South Carolina (MUSC) and South Carolina Pediatric Research Network (SCPPRN), Montefiore Medical Group (MMG) and University of Michigan Medicine Pediatric Primary Care Group. These rural, suburban, and urban practice groups commit to enrolling their over 60 separate pediatric practice sites, each with an associated HTN subspecialist(s), and we will open enrollment to other private and non-university affiliated practice groups before the project begins, potentially broadening this cohort further. Additionally, the project will recruit through and is supported by the Midwest Pediatric Nephrology Consortium, a national organization with 73 pediatric member centers, multiple NIH grants, and over 30 ongoing multi-center studies, whose goal is to "improve and promote high quality care of pediatric nephrology patients through . . . collaborative clinical and translational research." Nephrologists associated with the MWPNC will be able to identify practice groups who frequently refer to them, and suggest enrollment in this study. We ultimately consented 64 practices into the collaborative.

The main group of human subjects included in this research project are the adult physicians, nurses and office staff members whose behavior we will change to provide best-practice care for diagnosing and providing initial management for pediatric hypertension (HTN). We will collect pediatric patient HTN error data as a marker of this behavioral change but there will be no children directly involved in the research as study subjects. Please see attached consent form for each participating practice site. As this intervention is low to no-risk, represents standard of care and best practices that should be implemented regardless of this study, and data submitted to the research team is deidentified, we will request a waiver of consent for patient data access and have each practice site lead consent for their practice site's practitioners.

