**Figure 2: 28 month collaborative structure, Winter 2018-Spring 2020**

The 6 committed practice groups have over 1,000 providers and 1.5 million pediatric patient visits annually. Each practice group, including additional ones not yet recruited, will receive approximately \$5,000 annually to fund data collection processes. Each of the at least 60 practice sites will identify a multidisciplinary team consisting of at least one physician, nurse and practice associate, allowing for improvement across disciplines. Teams will be supported by a pre-identified relevant and local HTN subspecialist.

Similar to our current diagnostic error QIC, we will apply multivariate matching to practice groups before randomization, which has been shown to provide more accurate effect estimates, creating an equivalent of 7% increase in sample size. Practice groups will be matched based on key demographics including 1) patient volume per practitioner +/- 100 patients, 2) patient population (rural, suburban or urban), 3) number of clinic sites, and 4) prior work reducing HTN diagnosis and management errors. These data as well as baseline demographic data and prior quality improvement experience data will be collected annually via the BP-CATCH Practice Inventory (attached). It will be completed by the lead practice physician following submission of a signed consent form to participate in the BP-CATCH project. The survey tool will be collected via SurveyMonkey, and administered at the start of the project, and twice annually thereafter. Similarly, we will administer a demographic survey to the hypertension subspecialists for each practice group. It will be completed by the hypertension subspecialist physician following submission of a signed consent form to participate in the BP-CATCH project. The survey tool will be collected via SurveyMonkey, and administered at the start of the project, and twice annually thereafter. Data from this survey will not be used in randomization. After matching, randomization will occur via computerized random number generation and practice groups will be assigned to one of 2 study cohorts.

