### **6.2 Data Entry Errors and Missing Data:**

We will make every effort to minimize data recording errors by checking for outliers or abnormal values using frequency tables or graphical tools such as box plots. If noted, we will correct or check

the validity of those values and discuss with sites. Although we expect few by virtue of randomization, we will examine imbalances between groups with respect to baseline practice demographic characteristics and outcome measurements with standard statistical methods depending on the outcome scale and validity of normal distribution assumptions. If necessary, we will apply log-transformations for right-skewed data. We will include variables that are significantly different in the above statistical models to control for their potential confounding effects. Although we anticipate little missing data based on prior QICs, when noted, we will examine reasons for incomplete records. We will analyze available data as the primary analytic strategy since mixed-effects modeling is valid for missing at random data. However, if missing data rate is greater than 5%, we will also conduct sensitivity analyses applying a full conditional specification multiple imputation method which can apply to missing not at random data. We will compare results between available data analysis and multiple imputations data analysis.

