### **6.3 Power Analysis:**

Assuming a two sided alpha level of 0.05 and >80% power, we calculated the effect size we could detect for the HTN and EBP diagnostic and management error primary outcome measure, comparing the three intervention conditions to the control condition and each other using the above models, and the QIC methodology and preliminary data (D.2.B.) presented in this application. As the data structure is complex with multilevel hierarchy in addition to introduction of titrated interventions in a stepped-wedge fashion, we conducted simulations to estimate empirical power to seek a minimally detectable effect size. We allowed substantial variations of the outcome at all levels of site, practice, and months. Specifically, we took 73% as the baseline diagnostic error rate under usual care and set the ranges of the outcome expectation as +/-15% at each level; for example, at the site level, the baseline incorrect diagnostic error rates will range from 73%-15% to 73%+15%, and so on. In addition, we set the outcome correlations among 10 chart reviews per month per site at a relatively large ICC=0.5. We used uniform distributions to randomly generate outcome expectations at all levels, and used Park's algorithm^92 to randomly generate individual chart-level correlated binary outcomes with ICC=0.5 for a given month. We generated 1000 simulation data sets for each candidate minimal effect size laid out in a grid search fashion and fitted the generalized mixed-effects model with random effect for all levels and counted p-values <0.05 out of 1000 for each effect size on the grid. As a result, our study with at least 7 practice groups, at least 60 sites, two cohorts, three intervention doses in addition to usual care, 24 months, and 10 chart reviews per month per practice is powered (>80%) to detect as small as 3% point decrease in each step-up 'titrated' dose, i.e., per each level increase in intervention dosage. Therefore, we are adequately powered to detect any decrease larger than 9% from usual care to hub and spoke condition.

Given the HTN error reduction estimates derived from our preliminary data and prior QIC, we are confident that we are powered to detect statistically and clinically significant effects in our primary outcome measure across all three intervention conditions.

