The study will randomize primary care clinics and their associated pediatric subspecialists (nephrologist and/or cardiologist) to one of 3 groups. All groups will get the same quality improvement collaborative intervention in a stepped wedge fashion. The first group will begin working on improving measurement of blood pressure, recognition of elevated blood pressure, and initial steps towards hypertension diagnosis and management. After 6 months, they will incorporate their subspecialist into the collaborative, to improve communication between the primary and subspecialty care realms. Following those 6 months, we will encourage primary care practices to move further with a “hub and spoke” model; their subspecialist will serve as a “hub” for hypertension diagnosis and management questions, to multiple primary care clinic “spokes” who will be doing more and more hypertension care themselves. We anticipate this will benefit subspecialists as they can see more new patients, benefit patients who will not need to travel to a tertiary care center and get more rapid care, and finally primary care physicians who can bill for higher acuity visits and have greater patient continuity. Group 1 will spend the final 6 months of the project sustaining these improvements and changes. Group 2 will proceed similarly through this list with a 6 month “usual care” with data collection phase in the beginning and no sustain phase at the end. Group 3 will have a 12 month usual care phase and not have the intermediate phase where primary and subspecialty care practitioners work on communication and transition issues. Practices will be involved for a total of approximately 29 months as some initial pre-work is needed. We anticipate the collaborative will begin pre-work in winter 2018-2019.

Each practice will be asked to identify and track the care delivered for approximately 10 patients with elevated blood pressure readings (not ‘Elevated Blood Pressure’ diagnosis) each month. They will also join every 6 month video conference day-long learning sessions when they are intervening, and every month 1-hour long collaborative video conferences. Everyone involved can get Part 4 MOC credit, one on one QI coaching, and we hope (but cannot promise until enrollment is complete) to be able to provide some small amount of money to each site to reduce data collection burden.

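### Practice groups are randomised, but the primary model gives each group only a constant intercept; if groups drift apart between phases, the standard errors are too small

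*Protocol*

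**What the plan says.** **Unit and number.** Section 3 (text under Figure 2) matches first: "Practice groups will be matched based on key demographics". It then randomises: "randomization will occur via computerized random number generation and practice groups will be assigned to one of 2 study cohorts". The matching factors are patient volume per practitioner, setting, number of clinic sites, and prior work on hypertension errors. The cohort is described as "at least 60 pediatric primary care practice sites from at least 6, diverse practice groups", while the power calculation in Section 6.3 assumes "our study with at least 7 practice groups, at least 60 sites, two cohorts". Both counts are minimums, since "we will open enrollment to other private and non-university affiliated practice groups". The text later gives a final count of practices ("We ultimately consented 64 practices into the collaborative") but none of practice groups.

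**Model.** Section 6.1 specifies a mixed model with identity link. Site, practice group and month have random intercepts, and charts are correlated within a month at a practice. Adjustment covers baseline error rate, patient volume, staffing and prior work, in an open list. There is no term for practice group by phase. Setting and number of sites are not named.

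**Further covariates.** Section 6.2 adds: "We will include variables that are significantly different in the above statistical models to control for their potential confounding effects".

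**The concern.** In this design the effect is identified by comparing groups in different conditions in the same calendar phase, and by changes within groups across phases. A constant group intercept removes stable differences between groups. It does not remove, or count as uncertainty, a group getting better or worse than the others in one phase for reasons unrelated to its assigned condition.

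The Protocol makes such divergence plausible. Subspecialist involvement, which carries the second and third interventions, is organised by practice group. The six initial groups are said to use integrated EHRs, and tools are adapted locally (Sections 3 and 5). Sites in one group may then move together, so each extra site brings less information than the model credits. With few groups, these shared movements do not average out. What is at stake is a nominal 5% test that rejects more often than 5%, and intervals that are too narrow.

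**Working it through.** **Inputs (Section 6.3).** Baseline error rate 73%; uniform spread of ±15 points at each level; 10 charts per site-month with ICC 0.5; 60 sites; 24 months; two-sided 0.05. Dose by six-month phase (Figure 2): Cohort 1 is 1, 2, 3, 3 (sustain phase kept at 3); Cohort 2 is 0, 1, 2, 3. **Assumed:** group-by-phase SD s, which the document does not give; sites spread evenly over groups.

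**Variances.**
- Site-month mean: 0.73 × 0.27 × (1 + 9 × 0.5) / 10 = 0.1084.
- Each ±0.15 uniform level: 0.30² / 12 = 0.0075, an SD of 8.7 points.

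**Step 1: the plan's own figure.** Power at 3 points per step = Φ(0.03/SE − 1.96), with SE from generalised least squares on site-month means. For 7 groups:
- month effects independent within each site: SE about 0.009, power 90-92%;
- month effects per group: 76-79%;
- month effects shared by all sites: SE about 0.018, power 38-39%.

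The ranges reflect how 7 groups are split between cohorts. The stated >80% reproduces on the first reading only. Section 6.3 does not make clear which was used.

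**Step 2: type I error when the group-by-phase term is left out.** Let V be the covariance under the Section 6.1 model and J the matrix with 1 where two site-months share group and phase. The planned estimator is By with B = (X′V⁻¹X)⁻¹X′V⁻¹. Its reported variance is (X′V⁻¹X)⁻¹ and its actual variance is B(V + s²J)B′. Then

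type I error = 2Φ(−1.96 × SE reported / SE actual).

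Two examples with month effects shared, 6 groups, s = 5 points:
- Dose slope: 0.0180 / 0.0219 = 0.82; 2Φ(−1.61) ≈ 11%.
- QIC versus usual care: 0.0365 / 0.0538 = 0.68; 2Φ(−1.33) ≈ 18%.

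| Months, groups | Contrast | s = 0 | 3 | 5 | 8 points |
|---|---|---|---|---|---|
| 24, 6-7 | Dose slope | 5% | 7% | 10-11% | 18-19% |
| 24, 6-7 | QIC v usual care | 5% | 9-10% | 17-18% | 30-33% |
| 24, 12 | Dose slope | 5% | 6% | 8% | 12% |
| 24, 12 | QIC v usual care | 5% | 7-8% | 12% | 21% |
| 12, 6-7 | Dose slope | 5% | 6% | 7-8% | 11-12% |
| 12, 6-7 | QIC v usual care | 5% | 7% | 10-11% | 18-19% |

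If month effects are instead independent within sites, the reading that reproduces the stated power, the 24-month dose slope with 6-7 groups gives about 10%, 18-20% and 32-34% at 3, 5 and 8 points. The table is the milder case for that contrast.

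**Step 3: check by simulation.** Binary charts were generated with no effect, and the Section 6.1 random structure was fitted by REML with a z test (250-300 runs per cell, Monte Carlo error about 1.5-2.7 points). At 5 points, 7 groups gave 10-12% (dose slope) and 16% (QIC contrast); 6 groups gave 10% and 19%. Adding a group-by-phase random effect (7 groups, dose slope) gave 5.6%, 5.2%, 6.0% and 6.8% at 0, 3, 5 and 8.7 points.

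**Step 4: power with the term added.** With s = 5 points, 7 groups and shared month effects, simulated power at 3 points per step was about 30% with a z test and 15% with a t test on groups minus two degrees of freedom.

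**Step 5: matching and the covariate screen.** With 6 groups in 3 pairs, an unpaired t test rejects 5.0%, 3.1% and 1.6% of the time at pair correlations 0, 0.3 and 0.6. Adding a covariate only when it is imbalanced at p < 0.05 gives 3.0-5.1%. Neither inflates the error.

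**The case against.** The strongest reply is that the size rests wholly on a variance the Protocol never states. With none, the planned model is close to nominal. In the 6-group simulation the dose slope rejected 8% even at SD 0 and 10% at SD 5, a gap within Monte Carlo error, so part of any excess at small SDs may come from few groups and a z test. The drift mechanism is inferred: the text varies on whether subspecialists belong to sites or groups, and integrated EHRs need not mean one system per group. All of this stands, and it is why the figures are given as a range.

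Several stronger readings are tempting but unsupported:
- **That about 60 sites are treated as independently randomised.** The model has a practice-group intercept; only change over time within groups is missing.
- **That only 6 or 7 groups were randomised.** These are minimums, enrolment was open, and the final count is not stated.
- **That ignoring the matching and screening covariates make p-values too small.** Both were neutral or conservative in Step 5. Patient volume, prior work and baseline error rate are already in Section 6.1.
- **That no p-value below 0.25 is attainable.** That needs exactly three matched pairs (2 / 2³ = 0.25) and a randomisation test. The Protocol plans no such test and does not say that the matching is in pairs.
- **That small-sample degrees of freedom are wrongly omitted.** They may be in the statistical analysis plan, which is not at hand.
- **That clinics were the randomised unit.** A recruitment email says "The study will randomize primary care clinics and their associated pediatric subspecialists", but it describes a three-group design that differs from the two cohorts of Section 3.

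**Conclusion.** The point holds in a conditional form. The Protocol randomises practice groups, guarantees only a small number of them, and states a random structure that leaves out variation of groups between phases. If that variation exists, standard errors are too small; the table gives the size under assumed SDs of 0 to 8 points. For scale, the upper value lies just below the 8.7-point SD that Section 6.3 itself allows at each level. The inflation shrinks with more groups or with a shorter analysis, which matters because Section 3 now limits the collaborative's published results to data up to March 2020.

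The significance screen in Section 6.2 is a separate, lesser matter. It makes the primary model depend on the data. Leaving setting and number of sites out of the named covariates may also forfeit some of the precision that Section 3 claims for matching, put there at about a 7% gain in sample size.

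**What to change.** 1. State how many practice groups were randomised and to which cohort, and name the practice group as the randomised unit throughout.
2. Add a practice-group-by-phase random effect to the primary model in Section 6.1, and base tests and intervals on the number of practice groups. If the analysis plan already does either, refer to it.
3. Replace the significance screen in Section 6.2 with a fixed covariate list: baseline error rate and all four matching factors, including setting and number of sites.
4. Restate the Section 6.3 power figure under the revised model, saying how month effects were generated and which group-by-phase SDs were assumed.

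No new data are needed. The cost is wider intervals and, if groups drift, power below the stated >80% at 3 points per step: about 30% or 15% in the case worked in Step 4. If groups do not drift, little should change.

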Both cohorts will collect 3 months of retrospective baseline data collection before beginning the study. During the first six months of the intervention, the practice groups randomized to Cohort 1 will begin working on improving HTN practices within their clinic via a QIC, while the other cohort will act as a control (usual care) with data collection (**Specific Aim 1**). Cohort 1 will attend an initial 1-day interactive video webinar learning session where they will learn QI methodology, enhance and practice QI skills, identify local 30-60 day aims to improve local HTN practices and increase their understanding of pediatric HTN. They will also begin tracking data on a HTN registry and learn how to ensure accurate BP measurement is completed in their clinic. They will participate in QI coaching, monthly video conferences, and monthly mini-root cause analyses (Mini-RCA) (see below). Cohort

2 will submit control data and not receive centralized data feedback. They will also begin tracking data on a HTN registry and learn how to ensure accurate BP measurement is completed in their clinic.

During the second 6 months, Cohort 1 will integrate their HTN subspecialist into the QIC and focus on issues at the boundary of PCP and subspecialty care (e.g. pre-referral work-up, communication across providers, and time for next available appointment). Cohort 2 will begin improving HTN practices within their clinics via a separate but comparable PCP-only QIC, (**Specific Aim 2**). In the third 6 months, Cohort 1 will continue QIC components and implement a hub and spoke model, where the PCP diagnoses and provides definitive management for pediatric HTN with subspecialist support and Cohort 2 will engage their HTN specialist (**Specific Aim 3**). In the final six months, Cohort 1 will sustain their changes, illustrating the durability of these system changes even after QIC completion. Cohort 2 will continue their QIC with the hub and spoke model.

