This stepped wedge design allows for maximal improvement efforts across the largest number of practices while maintaining a rigorous, randomized design. Additionally it allows for the evaluation of the primary outcome comparisons (usual care versus local QIC without subspecialist versus QIC with subspecialist versus QIC with hub and spoke model) and secondary outcome comparisons: 1) change in collaborative effect for second wave participants (HTN error rates in Cohort 1 versus Cohort 2 during initial locally focused QICs), and 2) sustainability after hub and spoke model introduction (error rates in Cohort 1 in months 13-18 versus months 19-24). Figure 2. These secondary outcome comparisons will shed light on the effectiveness and sustainability of QICs and inform future QIC designs.

QIC intervention components closely mirror prior evidence on components integral to QIC success and prior QICs conducted by the research team. Prior research has shown that improving errors requires more than just EHR alerts, which is why a QIC intervention was chosen. Important components of the QIC include rapid data feedback on performance with benchmarking, which is crucial to behavior change of clinicians. The evidence-based Mini-RCA used in this and prior QICs, involve identifying an error monthly at each site, examining 15 standardized patient and systems factors that could have led to the error, and spreading systematic lessons learned to prevent future errors. The QIC's interactive video webinar format was successfully employed in our diagnostic error QIC and allows for greater participation by providers who do not have time to travel and can engage more team members. The bundle of evidence-based tools implemented by the collaborative to help reduce HTN diagnosis and management errors will involve work from our prior QIC, and utilize concepts such as standardization, visual workflows, family engagement, EHR and handheld decision support, and streamlined communication. As with any QIC, practice sites will adapt these tools, and develop new tools which will be quickly spread across the QIC to accelerate change and improve care delivery.

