## **6. Statistical Analysis**

### **6.1 Statistical Models:**

The primary independent variable will be interventions with titrated QIC dosage levels stepped-up from the control condition (usual care) with scale scores from 0 (usual care) to 3 (hub and spoke). The primary dependent variable will be the proportion of all incorrect diagnostic and management decisions completed per 100 patients with elevated BPs. The individual-level outcome will be binary (incorrect or correct care), and absolute risk difference will be the primary measure of intervention effects. As there will be a multilevel hierarchy in the data structure, we will apply generalized mixed-effects models with identity link for testing the primary hypothesis in terms of risk difference. Site-specific, practice group-specific, and month-specific intercepts will be considered random to take into account potential variations in outcomes at all such levels in addition to correlations of individual-level outcome nested within each month for each practice. We will test if each step-up of the interventions (QIC without subspecialist, QIC with subspecialist, and hub and spoke) as compared to the control condition significantly reduce incorrect diagnosis and management proportions. We will also make all pairwise comparisons among the four conditions including usual care. All analyses will be controlled for potential confounding effects including factors such as baseline error rates, patient volume, number and training of providers, nursing and office staff, and prior work improving these errors.

For the secondary analyses testing 1) time to care, 2) sustainability, 3) change in collaborative effect for second wave and 4) necessity of PCP and subspecialist integration before hub and spoke model introduction, we will use all relevant QIC data. Each of these hypotheses will be tested with appropriate contrasts between intervention effect and the relevant group and time in generalized mixed-effects regression models. Testing the sustainability will be based on a contrast within Cohort 1.

The main outcome will be presented with descriptive statistics, examining the percent of patients who accepted the HBPM and returned data in a timely manner. We will also analyze the concordance between in-clinic manual BP measurements and the HBPM measurement averages.

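### The second-wave comparison sets Cohort 1 in months 1–6 against Cohort 2 in months 7–12, so it cannot separate a wave effect from shared calendar change

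*Protocol*

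**What the plan says.** Section 3, after Figure 2, names two secondary comparisons that the design is said to support. One is a "change in collaborative effect for second wave participants (HTN error rates in Cohort 1 versus Cohort 2 during initial locally focused QICs"). The text says these comparisons are meant to guide the design of later collaboratives.

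The schedule is fixed in the same section. After matching, "practice groups will be assigned to one of 2 study cohorts". On the period before the intervention the protocol states: "Both cohorts will collect 3 months of retrospective baseline data collection before beginning the study". Then "During the first six months of the intervention, the practice groups randomized to Cohort 1 will begin working on improving HTN practices", "while the other cohort will act as a control (usual care) with data collection". "During the second 6 months, Cohort 1 will integrate their HTN subspecialist into the QIC", and in the same period "Cohort 2 will begin improving HTN practices within their clinics via a separate but comparable PCP-only QIC".

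Section 6.1 gives site, practice group and month random intercepts and states no fixed calendar-time term. It describes the intervention both as a score from 0 to 3 and as four conditions compared pairwise. For the secondary hypotheses, including the second-wave one, it says: "Each of these hypotheses will be tested with appropriate contrasts between intervention effect and the relevant group and time in generalized mixed-effects regression models".

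**The concern.** The stated target is a change in the effect of the collaborative, but the quantity defined for it is a comparison of error-rate levels in two windows six months apart. Cohort 2's first collaborative has no usual-care group alongside it, because Cohort 1 has by then moved to the collaborative with subspecialists. Anything that shifts error rates in both cohorts between the first and second half-year, such as uptake of the recently updated guideline or season, enters the contrast as if it were a wave effect. Adjusting for baseline error rate removes a difference in level between cohorts, not a shift over time.

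The conclusion at risk is whether later participants do better or worse in a collaborative. It is also a conclusion likely to be drawn. Section 3 commits to publishing the November 2018 to March 2020 data. Those 17 months, read as 3 baseline plus about 14 intervention months, contain both first-collaborative windows. The sustainability comparison (months 13–18 against 19–24) cannot be completed from them.

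**Working it through.** The protocol gives no effect size, power or sample size for this contrast, so there is no stated figure to reproduce.

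**1. Overlap of the windows.** Cohort 1: months 1–6, mean 3.5. Cohort 2: months 7–12, mean 9.5. No month is common, and the means are 6 months apart. A shared fall of b points per month with no wave effect moves Cohort 2 minus Cohort 1 by −6b: −3, −6 and −12 points for b = 0.5, 1 and 2 (assumed values).

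**2. Identification with months fixed and four conditions.** Let g be the cohort difference, t1, t2, t3 and tS the effects of local collaborative, subspecialist collaborative, hub and spoke, and sustain, and w the wave effect. Fixed months leave only the Cohort 2 minus Cohort 1 difference in each period:

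- Baseline: g
- Phase 1: g − t1
- Phase 2: g + t1 + w − t2
- Phase 3: g + t2 − t3
- Phase 4: g + t3 − tS

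That is five equations for six unknowns, and w cannot be separated from t2. The design-matrix ranks agree: 21 of 22 columns for 3 + 14 months and 32 of 33 for 3 + 24 months. Setting sustain equal to hub and spoke does not help (31 of 32 for 24 months).

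**3. The same with the 0–3 score.** If tk = kβ, Phase 1 gives g − β and Phase 2 gives g + β + w − 2β = g − β + w, so w is the Phase 2 difference minus the Phase 1 difference. The matrix has full rank (20 of 20 and 30 of 30), but only because equal steps are imposed. The hypotheses in section 2 imply unequal steps from the 73% usual-care rate:

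- 15% read as relative: 73, 36.5, 31.0, 26.4
- 15% read as points: 73, 36.5, 21.5, 6.5

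Fitting the score with fixed months over the 24-month design to these values, with a true wave effect of zero, returns a wave effect of −15.1 or −10.8 points.

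**4. The random-month model of section 6.1.** Inputs from section 6.3: ±15 points uniform at each level, so variance 0.30²/12 = 0.0075; ICC 0.5; 10 charts per site-month (17 at baseline, section 4). Assumptions: 60 sites, 8 practice groups split evenly between cohorts, an average error rate of 55% for the residual variance, 3 + 14 months, and a cohort term. The estimator is generalized least squares. The bias is the wave coefficient produced by the shared trend alone. With z = bias/SE, the false-positive rate is Φ(−1.96 − z) + 1 − Φ(1.96 − z). The protocol does not say whether the month effect is common to all sites or separate within each site, so the ranges cover both.

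| Shared fall per month | Raw contrast | Bias, four conditions | False-positive rate (nominal 5%) |
|---|---|---|---|
| 0.5 point | −3 | about 1–3 points | about 6% |
| 1 point | −6 | about 3–5 points | about 8–10% |
| 2 points | −12 | about 5–11 points | about 16–26% |

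Example, 1 point per month with a common month effect: bias −5.4, SE 8.2, |z| = 0.66, false-positive rate 10%.

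A shared 6-point drop starting at month 7 passes into the wave term in full (−6.0 points) under four conditions. In the 24-month design this was so at every month variance tried, from 0 to 0.03. Under the 0–3 score with random months the bias is smaller, about 2 points at 1 point per month.

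**5. Matched difference in changes.** Cohort 1 goes from its baseline months (mean −1) to months 1–6 (mean 3.5), a gap of 4.5. Cohort 2 goes from months 4–6 (mean 5) to months 7–12 (mean 9.5), also 4.5. A linear shared trend contributes −4.5b to each change and cancels. A 6-point drop at month 7 does not cancel: it adds 0 to Cohort 1's change and −6 to Cohort 2's.

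**The case against.** The strongest reply is that the protocol names a change in effect as its target, that the parenthesis only identifies the data, and that section 6.1 leaves the exact contrast to mixed models with baseline adjustment, a detail that an analysis plan may settle. This stands in part, since the raw level difference may not be the final analysis. But the protocol claims that the design supports the comparison. With four separate conditions, which the pairwise comparisons require, no analysis plan can separate wave from calendar phase without an added assumption.

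Two stronger readings are tempting and not supported. A reader might infer that the cohorts are never observed at the same time; they run side by side in every phase, and only the two compared windows differ in time. A reader might also infer that fixed months always make the wave term inestimable. Under the 0–3 score in section 6.1 it is estimable, though only through equal steps. Section 6.1 itself makes month random, so the fixed-month result shows that the obvious repair fails. It is not an error in the stated model.

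It is also fair that the trend is assumed. Two points per month would be a 34-point fall over 17 months without any intervention, which is an extreme case. At 0.5 point per month the false-positive rate is close to nominal. The comparison is secondary and carries no power claim or decision rule.

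**Conclusion.** Wrong as written. The contrast in section 3 does not measure a second-wave effect apart from shared change over time, and the model in section 6.1 does not repair this. The aliasing follows from the schedule alone and needs no assumption about trend. The size does depend on the assumed trend: anywhere from 1 to 11 points in the four-condition mixed model for shared falls of 0.5 to 2 points per month, and less under the 0–3 score. The documents do not show that such a trend occurred, so the point is that the claim cannot be supported, not that the result is known to be biased. The primary outcome is not affected by this point.

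**What to change.** In sections 3 and 6.1, withdraw the claim to test a second-wave effect. State that wave and calendar phase are confounded in this two-cohort design, and report the Cohort 1 and Cohort 2 first-collaborative error rates descriptively, with a confidence interval for their difference.

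As a supportive estimate, replace the level contrast with a difference in changes over equal calendar gaps: Cohort 1 months 1–6 minus its three baseline months, against Cohort 2 months 7–12 minus its own months 4–6. State its limits with it:

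- It removes only a linear shared trend, not seasonality or an abrupt shift.
- Its interval is wider.
- Cohort 1's change includes the start of the registry and blood pressure measurement training, whereas Cohort 2 began both in Phase 1, so its change does not. Cohort 1's reference months are also retrospective.

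The cost is one redefined secondary comparison on data already collected and the loss of a hypothesis test that the design could not support.
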